##### Cancer Treatment Cohort

We will use stratified random assignments to place patients in each arm of the trial. Once we have enrolled 10 patients with each type of cancer, we will randomly assign half to the ARROW program and the other half to the one-time education arm. All patients will have a minimum of 12 months of follow-up, and some will have up to 36 months of follow-up. Data will be collected at baseline and then annually for the 3-year duration of the trial from the AYA living with HIV through surveys and by abstracting information from the Cancer Diseases Hospital records. The sample size (n=500) was calculated using conventional specifications (α=.05; 2-sided tests) based on the primary end point and allowing for an absolute 15% point improvement; the estimated current level of adherence is 75%, which will increase to at least 90% with the ARROW program. With 50% (250/500) of the patients in each arm, we will have more than 90% power to detect this difference.

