##### Cancer Treatment Cohort

This will take place entirely at the Cancer Diseases Hospital, with some patients being recruited from the University Teaching Hospital. A total of 500 AYA living with HIV who have been diagnosed with CC, NHL, or KS will be recruited into the study, with 50% (250/500) of the patients in each trial arm (ie, one-time educational campaign vs the ARROW intervention). Patients will be surveyed annually at 12, 24, and 36 months. Trained data collectors will obtain consent and enroll AYA living with HIV, aged 15 to 39 years. We will be aiming for the following targets for each cancer type: 50% (250/500) of the participants with CC, 30% (150/500) of the participants with KS, and 20% (100/500) participants with NHL (with an overall equal number of male and female AYA living with HIV for KS and NHL). While AYA living with HIV who are pregnant will be excluded, as they require specialized care, those who become pregnant during the trial period will remain enrolled in the study; CC screening and physical examinations for KS and NHL will be offered based on Zambian guidelines pertaining to pregnancy.

We hypothesize that, by facilitating peer support to address barriers and gaps at multiple levels, the ARROW program will be more effective than the one-time education campaign, but more expensive as well. As shown in Figure 2, we will simultaneously conduct separate randomized controlled trials at the HIV treatment facilities and at the Cancer Diseases Hospital. The trials will be initiated upon completion of the preimplementation preparation activities. We will then embed PCs into the care teams at the HIV facilities and the Cancer Diseases Hospital and initiate the planned implementation activities of the ARROW Provider Network in the ARROW program arm. The comparison arm will receive the one-time education campaign: health care providers at the HIV facilities (particularly physicians and nurses) will receive a brochure with key guidance for early diagnosis of cancers in AYA living with HIV, and the AYA living with HIV upon recruitment will also receive education brochures at both the HIV facilities and the Cancer Diseases Hospital. The Health Care Collaborative will continue to meet as planned on a quarterly basis.

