##### Cancer Treatment Cohort

The primary end point is the proportion of those who are adherent to cancer treatment (complete all treatment modalities as prescribed; 2-week delays will be allowed) at 12 months after diagnosis, the secondary end point is the proportion alive at 12 months after diagnosis, and the tertiary end point is the proportion with recurrence at 24 and 36 months (among those with 24- and 36-month follow-up).

For all the AYA living with HIV, we will report adherence to ART (proportion of those filling prescriptions at least every 3 to 6 months) and viral load at 12, 24, and 36 months. Viral load testing is generally conducted at least annually for AYA living with HIV as part of routine guideline-recommended practice. We will reinforce the need for regular viral load testing as part of health care provider training and have set aside funds to conduct viral load testing for study participants for whom this information is unavailable in the medical record.

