## Results

Recruitment for both the early detection cohort and the cancer treatment cohort began in June 2024. Recruitment for the early detection cohort concluded in February 2025, and we have enrolled a total of 3442 individuals. Of these 3442 participants, 1731 (50.29%) were enrolled in the 9 facilities randomized to the intervention arm and 1711 (49.74%) were enrolled in the 9 facilities in the control arm. The ARROW intervention was launched at all intervention facilities by December 2024. Recruitment for the cancer treatment cohort began in July 2024 and is ongoing; as of March 2025, 105 individuals have been enrolled. Of these 105 participants, 52 (49.5%) are receiving the one-time educational campaign in the usual care arm and 53 (50.5%) are receiving the ARROW intervention. Hypothesis testing analysis, as well as cost-effectiveness and policy implication analysis, will be conducted. The 12-month end point results will be available in early 2026.

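### As written, cancer patients are assigned only once 10 of a type are enrolled while outcomes are timed from diagnosis; this dilutes the contrast and does not fit the reported 52/53 allocation

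*Protocol article*

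**What the plan says.** **Assignment.** Sample Size and Recruitment, Cancer Treatment Cohort, describes stratified random assignment and gives the rule: "Once we have enrolled 10 patients with each type of cancer, we will randomly assign half to the ARROW program". The other half go to the one-time education arm.

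**Who is enrolled.** Overall Study Design, Cancer Treatment Cohort: "A total of 500 AYA living with HIV who have been diagnosed with CC, NHL, or KS will be recruited into the study". The target mix is "50% (250/500) of the participants with CC, 30% (150/500) of the participants with KS, and 20% (100/500) participants with NHL". The same section has comparison-arm patients given their brochures at the time of recruitment.

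**Outcome and clock.** Study End Points, Cancer Treatment Cohort, defines adherence as "complete all treatment modalities as prescribed; 2-week delays will be allowed" and times it "at 12 months after diagnosis, the secondary end point is the proportion alive at 12 months after diagnosis". Table 2 gives the same timing for both end points.

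**Progress.** Results: "Recruitment for the cancer treatment cohort began in July 2024 and is ongoing; as of March 2025, 105 individuals have been enrolled". Of these, "52 (49.5%) are receiving the one-time educational campaign in the usual care arm and 53 (50.5%) are receiving the ARROW intervention".

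The article does not cap the time from diagnosis to assignment, and it does not say whether treatment is held until assignment.

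**The concern.** Under the written rule, enrolment precedes assignment, and everyone but the last patient in a batch waits. Because the clock starts at diagnosis, the wait uses up part of the 12-month window. The adherence definition tolerates delays of only two weeks, so one longer lapse during the wait could settle a patient's outcome before an arm exists. A death during the wait would likewise be beyond ARROW's reach. Such events would occur at the same rate in both arms and pull the observed difference below the planned 75% versus 90%, most for the cancer type that accrues most slowly.

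There is also a question of fact. Halving complete batches of 10 restricts the arm totals that can occur, and the reported totals are not among them. The published randomisation method may therefore not be the one in use.

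**Working it through.** **1. The plan's power figure.** Inputs from Sample Size and Recruitment: 75% versus 90%, 250 per arm, two-sided α = 0.05. With d the difference and p̄ the mean of the two proportions:

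power = Φ{[d − 1.96·√(2p̄(1−p̄)/n)] / √([p₁(1−p₁)+p₂(1−p₂)]/n)}

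Here d = 0.15 and p̄ = 0.825. The null term is 1.96·√(0.28875/250) = 0.0666, and the denominator is √(0.2775/250) = 0.0333. Power = Φ(0.0834/0.0333) = 99.4% (99.1% with continuity correction). The stated power of more than 90% is correct, with a wide margin: 133 per arm would give 90%.

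**2. Waiting time under the written rule.** Accrual is 105 patients in about 8 to 9 months (July 2024 to March 2025), or 13.1 to 11.7 per month. Multiply by 50/30/20 to get the rate r for each type. With steady arrivals and batches of 10, the first patient waits 9/r and the mean wait is 4.5/r.

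| Type | r per month | Mean wait (months) | Mean wait (weeks) | First patient (months) |
|---|---|---|---|---|
| Cervical cancer | 6.56–5.83 | 0.69–0.77 | 3.0–3.4 | 1.37–1.54 |
| Kaposi sarcoma | 3.94–3.50 | 1.14–1.29 | 5.0–5.6 | 2.29–2.57 |
| Non-Hodgkin lymphoma | 2.62–2.33 | 1.71–1.93 | 7.4–8.4 | 3.43–3.86 |

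Over all patients the mean is 1.03 to 1.16 months (4.5 to 5.0 weeks), about 9 to 10% of the 12-month window.

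Sensitivity:
- Results also gives June 2024 as the start for both cohorts. With 10 months of accrual, the lymphoma mean is 9.3 weeks.
- At an assumed faster pace of 500 in 24 months, the means are 1.9, 3.1 and 4.7 weeks.
- If the rule means that all three types must reach 10 before anyone is assigned, the slowest type sets the wait for everyone.

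**3. Effect on power.** The documents do not say what share of lapses falls before assignment, so the losses below are assumptions (control 75%, 250 per arm).

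| Share of effect lost | Difference (points) | Power |
|---|---|---|
| 0% | 15.0 | 99.4% |
| 10% | 13.5 | 97.6% |
| 20% | 12.0 | 93.0% |
| 30% | 10.5 | 84.1% |
| 40% | 9.0 | 70.4% |

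Power reaches 90% at about 11.4 points, a loss of 1 − 11.4/15 = 24%. If lapses were spread evenly over the 12 months, the mean wait would cost about 10% of the effect, leaving about 98% power. Lapses concentrated early in treatment would cost more.

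**4. The allocation.** Complete batches of 10 split 5:5 give an assigned total divisible by 10 and equal arms. The report has 105 assigned at 52 and 53; 105 is not divisible by 10 and the arms are unequal. With 105 enrolled over three types and at most 9 waiting in each, the rule would leave 5, 15 or 25 patients without an arm. The Results report none.

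**The case against.** The strongest reply is that the queue may not exist. All 105 patients already have an arm, and comparison-arm brochures are handed over at recruitment. Both fit assignment on entry, using blocks of 10 within cancer type, and three part-filled blocks can produce 52/53. On this view the sentence about 10 patients is a compressed description of blocking, and an article may leave the detail to the full protocol. This stands as a reason not to treat the waits as observed facts. It does not rescue the sentence, which states a different rule and contradicts two other places in the same article.

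Other parts of the reply also stand. Dilution acts alike in both arms, so no bias towards ARROW is shown. The share of the effect lost is assumed. At 250 per arm a 20% loss still leaves 93% power. Twelve months after diagnosis is a natural anchor and is stated consistently, so the choice of clock is not itself an error.

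A reader might go further and infer that power falls well below 80% because observed accrual points to fewer than 500 patients. A recruitment shortfall is a separate matter that the batch rule does not cause. A reader might also infer that patients are randomised after their outcome is known. The article does not describe what happens to someone who dies or stops treatment while waiting, and that treatment continues during the wait is itself an inference.

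**Conclusion.** The point holds for the rule as written. Followed literally, it leaves patients unassigned for a mean of about 3 to 8 weeks by cancer type, and for up to about 3.9 months for the first lymphoma patient in a batch, inside an outcome window that starts at diagnosis. These waits rest on steady arrivals, the target mix, and 8 to 9 months of accrual.

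The consequence is a diluted contrast of unknown size. The planned power survives unless more than about a quarter of the 15-point effect is lost. The documents do not support a claim that a substantial loss of power has occurred, or that unexposed time is in fact entering the end point.

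The conflict with the reported allocation needs no assumption beyond the rule itself: 105 patients at 52/53 cannot come from complete batches of 10 split in half. Either the method is misdescribed or it is not being followed.

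**What to change.** - Replace the batch rule with individual randomisation at consent, from a concealed list with permuted blocks of varying size, stratified by cancer type. Assigning a whole batch at once has the merit of protecting concealment, so the replacement list must be concealed from those who enrol.
- Keep the allocations already made, and state how the 105 were assigned. Reconcile the assignment rule in Sample Size and Recruitment with the brochure timing in Overall Study Design and the counts in Results. If patients were in fact assigned on entry within blocks, correcting the description is enough.
- Optionally, add a sensitivity analysis with adherence and survival counted from randomisation. The primary clock need not move.

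The cost is an amendment and a pre-generated list. Exact 5:5 balance in each batch becomes near balance, off by at most half a block per cancer type. Enrolment was still open at the last report, so most of the planned 500 could be assigned under the corrected rule.

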### Ethical Considerations

This study was approved by the institutional review boards at the Population Council (Protocol 1019) and the ERES (Excellence in Research Ethics and Science) Converge (Ref. No. 2022-Dec-003) and has been registered on ClinicalTrials.gov (NCT06004011). For the AYA living with HIV aged <18 years, we will obtain both written parental consent and assent from the minors. The AYA living with HIV aged ≥18 years will be asked to provide written informed consent. Trained data collectors will administer and document informed consent. Data will be collected via a secure data platform, and no identifiable data will be collected in the baseline and annual surveys. The participants will not receive monetary compensation for participation in study education sessions and other activities. The participants will receive ZK 100 (US $4.23) for completing the data collection at baseline and at annual touchpoints. This study also has a data safety monitoring board that provides ongoing evaluation of the study’s progress. This board has the authority to review any adverse events and provide guidance for any protocol modifications or termination of the study. The board comprises 5 members from nongovernmental organizations and the Zambian Ministry of Health. Any protocol changes, or other modifications, with be shared with the institutional review boards and the data safety monitoring board.

### Data Collection

In the HIV treatment facilities, we will generate electronic data files for the study cohort, and in other settings, such as referral facilities and the Cancer Diseases Hospital, the study team will abstract data from electronic databases or paper files. We will also conduct surveys to collect data from the AYA living with HIV and health care providers. The PCs will document their interaction with the AYA living HIV in the PC tracking tool, and the health care provider participation in the ARROW Provider Network will be captured in the study database. These details will be used to determine the “dose” of the ARROW program. All data will be collected by trained data collectors, who will undergo continual monitoring, and study coordinators, who will confirm fidelity to protocol specifications by random in-person review. Refer to Table 2 for the end point definitions and the biological, self-report, and clinical records data collected at baseline and at 12-, 24-, and 36-month follow-ups.

**Table 2 table2:** Data collection at baseline and at 12-, 24-, and 36-month follow-ups.

Constructs and measures		Instrument and specification	Source	Timing
**Data elements for primary, secondary, and tertiary end points: HIV and cancer care continuum**				
	Proportion of participants completing physical examination (KS^a^ and NHL^b^) and up to date with CC^c^ screening	Confirmation of services will be based on clinical records and PC^d^ tracking tool (primary end point at 24 mo)	Biological, imaging, and clinical procedures identified through clinical records and study database	12, 24, and 36 mo
	Proportion of participants completing diagnostic tests and initiating treatment in ≤90 d	Measured as days from referral for testing and cancer diagnosis, respectively; based on chart review and study data	Biological, imaging, and clinical procedures identified through clinical records and study database	24 and 36 mo
	Proportion of participants completing repeat examinations and screening at the recommended interval	Screening every 2 y for CC and annual examination (especially when CD4^e^<100) based on the Zambian guidelines	Biological, imaging, and clinical procedures identified through clinical records and study database	36 mo
	Proportion of participants with early-stage diagnosis^f^	Stage 1 or 2 for NHL and CC; good risk for KS^g^	Biological, imaging, and clinical procedures identified through clinical records and study database	36 mo
	Proportion of participants adherent to cancer treatment^f^	Complete cancer treatment modalities as recommended	Biological, imaging, and clinical procedures identified through clinical records and study database	12 mo after diagnosis
	Proportion of participants alive at 12 mo after diagnosis^f^	Follow-up conducted by PCs and entered in study database	Biological, imaging, and clinical procedures identified through clinical records and study database	12 mo after diagnosis
	Proportion of participants with recurrent disease^f^	AYA^h^ living with HIV and cancer who experience cancer recurrence	Biological, imaging, and clinical procedures identified through clinical records and study database	36 mo
	Proportion of participants adherent to ART^i^ and viral load	Prescription filled every 3 to 6 mo; blood test	Biological, imaging, and clinical procedures identified through clinical records and study database	Annually

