#### Individual Level

There is growing evidence on the role that peer support can play in addressing individual and interpersonal barriers to improve knowledge and encourage AYA to seek medical care [56-62]. We will place trained peer counselors (PCs) in HIV treatment facilities and at the Cancer Diseases Hospital to educate AYA living with HIV, provide emotional support, and offer care coordination and linkages with the clinical team. PCs will offer support for early diagnosis of cancers, completion of cancer treatment, and ART adherence as required. They will coordinate care with health care providers and serve as an extension of the clinical team by conducting physical examinations to identify signs of KS and NHL and offering coping strategies for ART and chemotherapy side effects.

A total of 21 PCs, 10 (48%) males and 11 (52%) females between the ages of 20 and 39 years, will be recruited. Of the 21 PCs, 18 (86%; 9/18, 50% males and 9/18, 50% females) will receive traning for placement in HIV treatment centers. The remaining 3 PCs (14%; 1/3, 33% male and 2/3, 67% females) will be posted to the Cancer Diseases Hospital. The recruitment of more female PCs is due to the heavy burden that CC places on the health care system. Our existing 3-week training curriculum, from a previous study [18] conducted by the research team, will be tailored for PCs and will include training on appointment tracking systems. The curriculum will include standardized operating procedures for implementing the group education sessions to include additional details on cancer risk, early diagnosis approaches, and optimal treatments. Those assigned to the Cancer Diseases Hospital will receive training on how to help AYA living with HIV manage treatment side effects and assist with their adherence to ART while undergoing cancer treatment. The PCs will conduct site visits of the HIV facilities and the Cancer Diseases Hospital to become familiar with the staff, the layout of the clinics, and the services available.

Table 1 summarizes the 4 core PC roles and their corresponding activities. The PCs will offer 6 group education sessions at each ARROW HIV facility per month (one module each month) for the first 12 months, along with one-on-one education. For the remaining follow-up period, PCs will offer one-on-one education as needed. All other activities will continue throughout the trial.

**Table 1 table1:** Key functions of peer counselors (PCs).

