##### Early Detection Cohort

We propose a cluster randomized study to be implemented at 18 HIV treatment facilities in Lusaka province. Three facilities serving each type of regional population (urban, periurban, or rural populations) will be randomly assigned to a study arm: the ARROW program or one-time education. Overall, 9 (50%) facilities will be assigned to each arm of the trial, with data collection at baseline and at 12-, 24-, and 36-month follow-up. At each of the 18 clinics, we will enroll 100 men and 100 females resulting in a total of 3600 participants in the early detection cohort. The 200 AYA living with HIV per facility will be selected by first reviewing the HIV register and identifying those who meet the study inclusion criteria: 15 to 39 years of age, on ART for at least 6 months, not pregnant, and with no pending plans to move from the current residence during the 3-year study duration. For all the 3600 participants, we will collect baseline data and capture information on study end points from the SmartCare system, and the supplemental data will be collected by PCs and trained study data collectors (eg, tracking referrals for all participants and obtaining results of biopsies).

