#### Sample Size and Recruitment

##### Early Detection Cohort

We will use stratified random sampling to select an equal number of male and female participants and a mix of AYA living with HIV with perinatally and behaviorally acquired HIV. In terms of age distribution, 20% (720/3600) of the sample will be aged 15 to 19 years, 20% (720/3600) will be aged 20 to 24 years, and 60% (2160/3600) will be aged 25 to 39 years. We will oversample AYA living with HIV in each stratum to account for AYA living with HIV who may not meet inclusion criteria or who decline to participate. HIV facility staff will contact AYA living with HIV or consenting adults (for those aged 15 to 17 years) to discuss the study, and those interested will meet with trained data collectors who will assess eligibility and obtain consent or assent. The sample size was calculated assuming conventional specifications (α=.025 for each end point, 2-sided tests) based on the dual primary end points and allowing for the detection of an absolute 20% point improvement in the primary end points, which is our minimum threshold to consider the ARROW program successful. For the one-time education arm, given the current low level of uptake of early diagnosis services, we estimate uptake of physical examinations to be about 15% (15/100) and CC screening to be about 20% (20/100) at 12 months. With our proposed sample size of 3600, we will be able to detect a 20% difference in uptake of physician examination (35% in the ARROW arm) with over 90% power and CC screening (40% in the ARROW arm) with over 85% power. We can achieve this even after accounting for up to 10% attrition at 12 months (a previous study conducted by the research team achieved this retention rate without the level of active participant contact planned for this study) [67]. We estimate that the interclass correlation coefficient will be in the range of 0.03 to 0.05 because correlation coefficients for binary data are typically quite small, especially when physical examinations and screening uptake are very low [68].

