### Limitations and Approaches to Minimize Bias

First, although cluster randomization reduces contamination across study arms, it increases the risk that the AYA living with HIV in each arm may differ at baseline. The study sampling frame, based on the HIV registers, will allow us to assess baseline differences before facility randomization and adjust our sampling process with propensity score weights. Second, data could be missing because of nonresponse and study attrition. The PCs will maintain regular contact with the AYA living with HIV, and we will use rigorous field data collection practices, including training data collectors, developing protocols, and monitoring fidelity continually. Furthermore, we will address any missing data by including demographic covariates that will serve as proxies for dropout and conducting sensitivity analyses. Third, we anticipate health care provider turnover at the HIV treatment facilities and will conduct refresher training sessions as needed throughout the trial period.

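### The 12-month examination and screening end point may be counted from a peer-counselor log that appears to exist only in the ARROW arm, and no common procedure is fixed for tracing 12-month survival

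*Protocol article*

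**What the plan says.** Data Collection names Table 2 as the place for the end point definitions.

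- **Examination and cervical screening.** The row for participants examined for KS and NHL and up to date with screening reads "Confirmation of services will be based on clinical records and PC^d^ tracking tool (primary end point at 24 mo"). The 24 months in that cell conflicts with the 12 months under Study End Points; that is a separate matter.
- **Survival at 12 months (cancer treatment cohort).** The specification is "Follow-up conducted by PCs and entered in study database". The source column adds clinical records and the study database.
- **The tool.** Data Collection says "The PCs will document their interaction with the AYA living HIV in the PC tracking tool", and uses these entries to measure the dose of ARROW.
- **The PCs.** Under Individual Level they run the sessions at ARROW facilities and "serve as an extension of the clinical team by conducting physical examinations to identify signs of KS and NHL". Randomized Controlled Trials describes embedding them in care teams as part of starting ARROW, while the comparison arm receives brochures. Implementation Outcomes counts all PCs among those implementing ARROW and none in the comparison arm.
- **Retention.** The limitations section says "The PCs will maintain regular contact with the AYA living with HIV".
- **Text covering both arms.** For all 3600 early-detection participants, end points come from SmartCare, and "the supplemental data will be collected by PCs and trained study data collectors", with referral tracking for all participants as an example. Data Collection says trained data collectors collect all data.

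**The concern.** If the tool exists only where PCs work, a service that was given but never entered in the clinical record can be recovered in ARROW and is lost in control. Recorded uptake would then differ with no difference in care. The planned analyses (GEE, covariate adjustment, propensity scores) act on clustering and baseline imbalance. They cannot correct outcome misclassification that differs by arm. The people keeping the log also deliver the intervention, including the examination being counted.

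At stake are the size of the primary effect, its type I error, and how the result is judged against the 20-point threshold for success. For survival the issue is comparability: the article names who follows patients but not who follows those in the control arm.

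**Working it through.** **1. The plan's own power.** Inputs from Sample Size and Recruitment: 9 facilities per arm, 200 per facility (100 women), 10% attrition, ICC 0.03-0.05, two-sided alpha 0.025 (z = 2.241).

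Effective n per arm = 9m / [1 + (m − 1)·ICC].

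- Examination, m = 180: 1620/9.95 = 162.8 at ICC 0.05; 1620/6.37 = 254.3 at ICC 0.03.
- Screening, m = 90: 810/5.45 = 148.6 at ICC 0.05; 810/3.67 = 220.7 at ICC 0.03.

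Power for 15% v 35% is 97.6-99.9%, and for 20% v 40% it is 94.0-99.2%. The stated figures (over 90% and over 85%) hold. Sample size is not the problem.

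**2. Differential capture with no true effect (assumed rates).** The documents give no capture rates. Assume the same true uptake p in both arms, ARROW capture 95%, control capture s = 80% or 70%.

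d = p(0.95 − s); SE = √{[pA(1 − pA) + pC(1 − pC)]/n}, with pA = 0.95p and pC = s·p.

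False-positive probability = Φ(d/SE − 2.241) + Φ(−d/SE − 2.241).

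| p | s | Recorded, ARROW v control | d (points) | ICC 0.05 | ICC 0.03 |
|---|---|---|---|---|---|
| 25% | 80% | 23.8% v 20.0% | 3.8 | 7.9% | 11.2% |
| 25% | 70% | 23.8% v 17.5% | 6.3 | 20.0% | 31.1% |
| 35% | 80% | 33.3% v 28.0% | 5.3 | 11.3% | 17.0% |
| 35% | 70% | 33.3% v 24.5% | 8.8 | 31.2% | 47.9% |

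Example, first row at ICC 0.05: SE = √[(0.2375·0.7625 + 0.20·0.80)/162.8] = 0.0458; d/SE = 0.82; Φ(−1.42) + Φ(−3.06) = 0.079. The nominal value is 2.5%.

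**3. Effect on the success threshold.** Suppose 35% v 15% is recorded, with full capture in ARROW and capture s in control. The true difference is 0.35 − 0.15/s: 18.3 points at s = 0.9, 16.2 at 0.8 and 13.6 at 0.7. A recorded 20 points could then stand for less than 20.

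**4. Survival: direction.** Assume equal true survival S of 70-80%, with status unknown in 2% of ARROW and 10% of control.

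- Unknown counted as not alive: S(0.10 − 0.02) = +5.6 to +6.4 points for ARROW.
- Unknown counted as alive: −(1 − S)(0.10 − 0.02) = −2.4 to −1.6 points.
- Complete cases, all unknowns dead: S/0.98 − S/0.90 = −6.3 to −7.3 points.

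The sign depends on how unknown status is handled.

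**The case against.** **Coverage of both arms.** SmartCare is used for everyone, data collectors work in both arms, referrals are tracked for all participants, and every end point row in Table 2 lists clinical records and the study database. That PCs work only in ARROW is inferred: 18 facility PCs fit two at each of 9 ARROW facilities, but also one at each of 18. This stands as a limit on certainty and size. It does not remove the PC tool from the end point rule, and no sentence sets one procedure for both arms. If PCs do collect control data, intervention staff are ascertaining outcomes in both arms, which also needs stating.

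**Delivery is not detection bias.** An examination that a PC really performs is part of the intervention, and counting it is a treatment effect. This stands. The point concerns only services counted in one arm because of an extra log. It gives no reason to restrict the analysis to clinician-performed examinations.

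**Stronger readings that the documents do not support.**

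- A reader might infer that survival and retention are also biased towards ARROW. Better tracing finds deaths as well as survivors (step 4). On retention, the article also lists field practices, covariates for dropout and sensitivity analyses, and pays participants for annual data collection without limiting this to one arm.
- A reader might take "detect a 20% difference in uptake of physician examination" as a competing end point definition. The surrounding text speaks of physical examinations, so it is probably a wording slip.
- A reader might extend the point to every end point. Only the examination and screening row names the PC tool; diagnostic follow-up uses chart review and study data, and treatment adherence names no PC source.

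**Detail left to the full protocol.** Tracing steps often are. But Table 2 does not leave the source open; it names one that looks arm-specific.

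**Conclusion.** The point holds in a limited form. As written, the examination and screening end point draws on a source that most likely exists only in ARROW, and any resulting bias favours ARROW. For 12-month survival and for retention, follow-up may differ by arm, in a direction the documents do not determine.

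The size is unknown. Under the assumed capture rates the spurious difference is 3.8-8.8 points, with a false-positive probability of about 8-31% at ICC 0.05 and 11-48% at ICC 0.03. These figures use a normal approximation and depend entirely on the assumed rates; if capture is equal in both arms the problem disappears. A bias of this size would not produce a 20-point success from a null effect, but it would inflate the estimate and the type I error. Because it touches a primary end point and the planned analyses cannot repair it, it should be settled before the 12-month analysis, with results due in early 2026.

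**What to change.** 1. Define the primary examination and screening end point from sources available equally in both arms: SmartCare, clinic records and referral-facility records, abstracted by the study data collectors on the same schedule.
2. Count a PC-performed examination when it is entered in the clinical record. Keep the PC tool for dose and fidelity.
3. Report a sensitivity analysis that adds services logged only in the PC tool.
4. Have the data collectors establish 12-month vital status by the same tracing steps in both arms, and state how unknown status is handled.
5. State where PCs work and whether they collect any control-arm data.

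Cost: an amendment to the end point definitions and some data-collector time for tracing. SmartCare already covers the early detection cohort, and study staff already abstract records. The downside is that genuine services logged only in the PC tool leave the primary count, so the ARROW rate may be somewhat lower; the sensitivity analysis shows by how much. One difference may remain: PCs help results reach the HIV care team, so records could still be more complete in ARROW. Patient care does not change.
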